**Fig 1 pone.0263152.g001:**
[figure not shown]
Schedule of enrolment, interventions, and assessments. *Sociodemographic, clinical, and lifestyle characteristics. **Primary outcome: Pain intensity and functional limitation. Secondary outcome: Neuropathic-like symptoms, sciatic neurodynamic, conditioned pain modulation, and psychosocial factors. ***Adherence assessment, serious adverse events and adverse events, and assessment of patient satisfaction.

### Statistical analysis

#### Sample size calculation

The sample size calculation was performed a priori in the G*Power software version 3.1 (Heinrich-Heine-Universität, Düsseldorf, Germany) to determine a sufficient sample size. An estimated small effect size of 0.2 [73] in a repeated-measures analysis of variance (ANOVA) was considered to detect the between-groups difference for leg pain intensity (NPRS) and functional limitation (PSFS), with a statistical power of 90% and an alpha of 0.05 (5%), including 2 groups and 3 evaluations (initial, 5 weeks and 10 weeks) and a possible post-randomisation exclusion of 15% [74]. Based on the mentioned assumptions, the estimated sample size was 105 participants per group. A total of 210 participants will be included in the present study.

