### Outcomes measures

The primary outcomes will be leg pain intensity and functional limitation. Secondary outcomes will include neuropathic symptoms, sciatic neurodynamic, pain modulation, and psychosocial factors (detailed in S2 File). The follow-ups will be performed in 5 weeks, 10 weeks, and 26 weeks after randomisation. The follow-up assessment at 10 weeks after randomisation will be considered the primary time-point. In addition, adverse events and patient satisfaction will also be assessed.

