#### Primary outcome

*Pain intensity*. Pain intensity will be measured using the Numeric Pain Rating Scale (NPRS) from 0 (no pain) to 10 (worst pain possible). Participants will be asked to rate their leg pain and low back pain intensity at the evaluation moment. The NPRS is a common scale in pain studies, including those with sciatica and has good reproducibility levels [46]. The minimally clinically important difference considered in the current study will be an effect size of 0.2. The duration of pain will be recorded in months.

*Functional limitation*. Functional limitation will be investigated using the Patient-Specific Functional Scale (PSFS). The PSFS is a self-reported measure widely used to assess limited functional activities in patients with musculoskeletal disorders, presenting excellent reliability [47]. Participants will be asked to identify up to three important activities they are unable to perform or are restricted as a result of their pain. Each activity will be classified on an 11-point Likert scale regarding the current level of difficulty, which 0 means “unable to perform activity” and 10 “able to perform activity at the level as before injury”, and the mean of the three activities will be calculated. PSFS has ease applicability and can be used clinically as an outcome measure [48, 49].

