#### Primary analysis

The between-group differences for the primary outcomes considering the change in pain intensity and functionality from baseline to each 5, 10- and 26-weeks after randomisation will be calculated using mixed linear models using the interaction terms of treatment group versus time. The pain intensity and functionality will be investigated in separate models.

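### The sample-size section claims 90% power for a small effect size of 0.2, but the 10-week change contrast that the trial tests does not have it at 0.2 SD, and at 0.4 SD only if the correlation is high enough

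*Protocol article*

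**What the plan says.** The Sample size calculation section of the protocol article gives the route ("The sample size calculation was performed a priori in the G*Power software version 3.1") and the target: "An estimated small effect size of 0.2 [73] in a repeated-measures analysis of variance (ANOVA) was considered to detect the between-groups difference". The other inputs are 90% power, alpha 0.05, two groups, three evaluations (baseline, 5 and 10 weeks) and a 15% allowance for loss. The result is 105 per group, 210 in all. The section does not say which G*Power repeated-measures test was run, in which metric the 0.2 is expressed, or what correlation between measurements was assumed.

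Three other statements bear on this figure:

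- Outcomes measures: "The follow-up assessment at 10 weeks after randomisation will be considered the primary time-point".
- Primary analysis: change from baseline to each follow-up, estimated by "mixed linear models using the interaction terms of treatment group versus time".
- Primary outcome, under pain intensity: "The minimally clinically important difference considered in the current study will be an effect size of 0.2". Again no metric is given.

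**The concern.** A sample-size statement should describe the power of the test on which the trial will be judged. Here the primary result is the between-group difference in change at 10 weeks. The calculation is described only as a repeated-measures ANOVA for a between-groups difference over three evaluations, one of them baseline. G*Power's default for that description averages the group difference over all measurements, which is a different quantity.

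The bare 0.2 adds a second difficulty. G*Power's ANOVA routines take Cohen's f, whereas many readers will take a small effect size of 0.2 as 0.2 SD. The two differ by a factor of two when there are two equal groups. Because the same 0.2 is also the minimally important difference for pain, the ambiguity carries over into how the result will be interpreted. A neutral result could be taken to rule out a small effect with 90% power when the design cannot support that.

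**Working it through.** **Inputs.** From the Sample size calculation section: effect size 0.2, power 90%, alpha 0.05 (an F test, so equivalent to two-sided), 2 groups, m = 3 measurements, 15% loss, 210 randomised. From Outcomes measures and Primary analysis: 10 weeks, change from baseline, group-by-time. Assumed here: correlation ρ = 0.5 (range 0.3 to 0.7), equal SD at each visit, and 178 evaluable (89 per arm).

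**Step 1: reproduce 210.** For the between-factors test the noncentrality is λ = f²·N·m / [1 + (m − 1)ρ], with 1 and N − 2 degrees of freedom. With f = 0.2, m = 3 and ρ = 0.5, λ = 0.04 × 3N / 2 = 0.06N.

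- N = 176 gives power 0.898; N = 178 gives 0.9015.
- 178 / 0.85 = 209.4, rounded up to 210. This matches the protocol.
- Other correlations with the same test give 106 (ρ = 0), 170 (0.3), 231 (0.6) and 252 (0.7).
- Group-by-time interaction options at f = 0.2 without a sphericity correction give 56, 160 or 162, which become 66, 189 or 191 after the 15%. The MANOVA option gives 377 after the 15%.

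**Step 2: what f = 0.2 means.** For two equal groups f = d/2, so f = 0.2 is d = 0.4 SD. Entering d = 0.2 (f = 0.1) in the same test would have needed 704 evaluable.

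**Step 3: what the reconstructed test needs.** It tests the average difference over baseline, 5 and 10 weeks. Randomised groups have expected difference zero at baseline. If the true difference is 0.4 SD at both 5 and 10 weeks, the average is (0 + 0.4 + 0.4)/3 = 0.267 SD, so f = 0.133, λ = 0.133² × 178 × 1.5 ≈ 4.75, and power is 58%.

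**Step 4: power of the 10-week contrast.** The noncentral t has noncentrality d / [s·√(2/89)] and 176 degrees of freedom. For change from baseline s = √[2(1 − ρ)]; for a baseline-adjusted comparison s = √(1 − ρ²), in SD units. At ρ = 0.5, s = 1 for change, so the noncentrality is 0.2/0.150 = 1.33 at 0.2 SD and 2.67 at 0.4 SD.

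| True effect at 10 weeks | Analysis | ρ = 0.3 | ρ = 0.5 | ρ = 0.7 |
|---|---|---|---|---|
| 0.2 SD | change | 20% | 26% | 40% |
| 0.2 SD | baseline-adjusted | 29% | 34% | 46% |
| 0.4 SD | change | 61% | 76% | 93% |
| 0.4 SD | baseline-adjusted | 79% | 87% | 96% |

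With no loss at all (105 per arm), change at ρ = 0.5 has 30% and 82%. The most favourable case tried at 0.2 SD (105 per arm, adjusted, ρ = 0.7) has 52%. A global interaction test over three visits at ρ = 0.5, with the effect present at both follow-ups, has 26% at 0.2 SD and 79% at 0.4 SD.

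**Step 5: effect detectable with 90% power, 89 per arm.** The noncentrality needed is about 3.26, so d = 3.26 × s × 0.150. At ρ = 0.5 this is 0.49 SD for change (s = 1) and 0.42 SD with baseline adjustment (s = 0.866).

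**The case against.** Four points can be made for the plan.

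First, a reader might infer that 210 certainly came from the between-factors test. The documents do not establish this. An interaction test under G*Power's Cohen option with a non-sphericity correction of 0.87 also needs 178, hence 210. The between-factors route is the simpler explanation, since it uses default settings and fits the section's reference to a between-groups difference, but it remains an inference. If an interaction test was used, the averaging over baseline and the 58% fall away. Step 4 does not depend on the route.

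Second, a reader might infer that the trial has 26% power at its own target. That holds only if 0.2 means 0.2 SD. If 0.2 is Cohen's f throughout, both the design target and the important difference for pain are 0.4 SD. The text never says which, and the source cited for 0.2 is not available here. What stands is that reading 0.2 as f rescues the arithmetic only by making the effect 0.4 SD, which is hard to square with calling it small.

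Third, the 76% at 0.4 SD is not a firm shortfall. It belongs to ρ = 0.5, 89 per arm and an unadjusted change contrast. Power is 84% at ρ = 0.6 and 93% at ρ = 0.7, and 87% with baseline adjustment at ρ = 0.5. This objection stands in full, and the 0.4 SD result has to be given as a range.

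Fourth, details of the model may be in an analysis plan that is not shown. That could settle baseline adjustment, but it would not correct the power claim published in the protocol.

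**Conclusion.** The point holds in conditional form. The stated 90% power for a small effect size of 0.2 is not a property of the 10-week change contrast. At 0.2 SD power is 20–40% for change and 29–46% with baseline adjustment (89 per arm, ρ 0.3 to 0.7), and no variant tried exceeds 52%. At 0.4 SD, the effect that f = 0.2 represents, the ranges are 61–93% and 79–96%, so whether 90% is reached turns on a correlation that the protocol does not state.

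The mismatch between a repeated-measures ANOVA sized on three evaluations including baseline and a 10-week group-by-time contrast is only as certain as the inference about which G*Power test was used. The low power at 0.2 SD does not rest on that inference. Nor do the documents show that 210 is the wrong number of patients: it may be adequate for a moderate effect. What is wrong is the effect for which 90% power is claimed.

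**What to change.** Keep 210 randomised and rewrite the Sample size calculation section around the 10-week contrast. It should name the G*Power test, the effect-size metric (which only the authors can confirm), the assumed correlation and the evaluable number. Because the Primary analysis section describes change from baseline and mentions no baseline adjustment, the unadjusted figure should come first. For example:

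*With 210 randomised and 178 evaluable, and an assumed baseline-to-10-week correlation of 0.5, the trial has 90% power to detect a between-group difference of 0.49 SD in change from baseline at 10 weeks (0.42 SD if the model adjusts for baseline).*

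Remove the claim of 90% power for a small effect of 0.2. In the Primary outcome section, state the metric of the 0.2 given as the minimally important difference for pain, consistently with the sample-size section.

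The cost is rewording in two places and a less favourable stated detectable effect, with no added patients and no change in conduct. If the authors prefer to hold the target instead, 90% power on the change contrast at ρ = 0.5 with 15% loss needs about 312 randomised for 0.4 SD (234 with baseline adjustment) or about 1,238 for 0.2 SD (930 with adjustment).

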#### Data analysis

All data will be stored in a Microsoft Excel spreadsheet (Microsoft Corporation) and made available for statistical analyses. Data analysis will be performed by intention-to-treat using multiple imputation technique for missing data analysis and conducted by an independent and blinded examiner. The reasons for missing data will be reported. The demographic and clinical variables of the study population will be presented as mean and standard deviation for continuous variables. Categorical variables will be presented as absolute values and percentage. For continuous variables, the normal distribution of the study outcomes will be verified by the Shapiro-Wilk test. A significance level of less than 5% (p < 0.05) will be considered for all analyses. The statistical analysis will be performed using JASP version 0.10.2.0, and graph analysis will be performed using GraphPad Prism software (GraphPad Software version 8.00 for MacBook, San Diego, CA, USA).

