## Abstract

Advice to stay active is the primary management strategy for sciatica. Other conservative treatments such as neural management techniques may also contribute to sciatica recovery, but currently, the effects have not been robustly assessed. Thus, the aim of this study is to compare the effects of adding neural management to advice to stay active versus advice to stay active alone in improving pain intensity and functional limitation. Secondarily, to compare the effects of the experimental intervention in the sciatic neurodynamic, pain modulation, and psychosocial factors. A parallel-group, controlled, examiner-blinded superiority clinical trial randomised at a 1:1 allocation will be conducted in 210 participants with chronic sciatica. Patients will be recruited from outpatient physiotherapy clinics and community advertisements. The experimental group will receive neural mobilisation techniques and soft tissue mobilisation techniques for 30 minutes per session, 10 weekly sessions, plus advice to stay active on their activities of daily living, information on physical activity, imaging tests, and sciatica for 5 biweekly sessions lasting 25–30 minutes. The control group will receive advice to stay active only. The re-evaluation will be performed out after 5 weeks, 10 weeks, and 26 weeks after randomisation and primary endpoints will be pain intensity and functional limitation at 10 weeks. Secondary outcomes will include neuropathic symptoms, sciatic neurodynamic, pain modulation, and psychosocial factors. Adverse events and patient satisfaction will be assessed. Ethical approval has been granted from an Institutional Human Research Ethics Committee.

**Trial registration**: Trial was prospectively registered in the Brazilian Registry of Clinical Trials (number: RBR-3db643c).

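### Two unranked primary outcomes are each tested at p < 0.05 with no rule for combining them, so the 5% alpha and 90% power of the sample size cannot both hold for the trial's conclusion

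*Protocol article*

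**What the plan says.** Under Outcomes measures the protocol states: "The primary outcomes will be leg pain intensity and functional limitation". The same section fixes one primary visit: "The follow-up assessment at 10 weeks after randomisation will be considered the primary time-point". The Abstract agrees: "primary endpoints will be pain intensity and functional limitation at 10 weeks". There are therefore two primary endpoints at one time-point, and neither is placed ahead of the other.

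The Primary analysis section gives each endpoint its own mixed linear model: "The pain intensity and functionality will be investigated in separate models". The Data analysis section then sets the threshold for everything: "A significance level of less than 5% (p < 0.05) will be considered for all analyses".

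The Sample size calculation section makes one calculation for both outcomes. It uses "An estimated small effect size of 0.2" in a repeated-measures ANOVA with two groups and three measurements, alpha 0.05, power 90% and a 15% allowance for loss. The result is 105 per group, 210 in total. Alpha is not divided between the outcomes. The protocol states no hierarchy, no adjustment, and no rule on whether one or both outcomes must be significant.

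**The concern.** A superiority trial with two primary outcomes needs a rule that turns two p-values into one conclusion. Without it, two readings remain open, and they have different operating characteristics. If a significant result on either outcome is enough, there are two chances of a false positive, and the 5% in the sample size section does not cover the trial's claim. If both are needed, the 5% is safe, but the 90% describes each outcome alone and not the chance that the trial succeeds.

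Unless the two tests are perfectly correlated, one of the two planning figures therefore fails at trial level under either reading. If the choice is left until the results are known, it can be made to suit them. A trial that is significant on pain but not on function could be reported as positive or negative with equal support from the protocol.

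**Working it through.** **Inputs from the protocol.** Two primary outcomes and one primary time-point (Outcomes measures); separate models (Primary analysis); 0.05 for every analysis (Data analysis); effect size 0.2, two groups, three measurements, alpha 0.05, power 90%, 15% loss, total 210 (Sample size calculation).

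**Assumed inputs.** The correlation between the two week-10 test statistics is not given, so a range is shown. The correlation between repeated measurements in the sample size is not given either; 0.5 is assumed. The effect size of 0.2 is taken as Cohen's f.

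**1. The plan's own figure.** For the between-groups test in a repeated-measures ANOVA, the noncentrality is λ = f² × N × m / (1 + (m − 1)ρ), with 1 and N − 2 degrees of freedom.
- N = 178: λ = 0.04 × 178 × 3 / (1 + 2 × 0.5) = 10.68, power 0.9015.
- N = 176: λ = 10.56, power 0.898, just short of 90%.
- Allowing for loss: 178 / 0.85 = 209.4, rounded up to 210.

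This matches the stated 210 exactly, so the sample size arithmetic is not in question. It uses alpha 0.05 for a single test.

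**2. Either outcome suffices.** With no effect on either outcome and independent tests, P(at least one p < 0.05) = 1 − 0.95² = 0.0975. For correlated tests, the same probability comes from a bivariate normal distribution with two-sided limits of ±1.96:

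| Assumed correlation | False positive rate |
|---|---|
| 0 | 9.75% |
| 0.3 | 9.5% |
| 0.5 | 9.1% |
| 0.7 | 8.3% |
| 0.8 | 7.8% |
| 0.9 | 7.0% |
| 1 | 5% |

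**3. Both outcomes required.** With no effect on either outcome, the error is 0.05² = 0.25% if the tests are independent. It rises to 5% at perfect correlation and never exceeds 5%. Power is what changes. With 90% for each outcome, joint power is the bivariate normal probability that both statistics fall on the successful side:

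| Assumed correlation | Joint power |
|---|---|
| 0 | 0.9² = 81.0% |
| 0.3 | 82.2% |
| 0.5 | 83.2% |
| 0.7 | 84.7% |
| 0.8 | 85.6% |

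**4. Cost of controlling the either-outcome claim.** Using step 1 with N = 178 and λ = 10.68, but alpha 0.025, power is 84.2% against 90.2% at 0.05. Two tests at 0.025 each give 1 − 0.975² = 4.94% if independent, and less with positive correlation. Holm's procedure keeps the 5% limit and tests the second outcome at the full 0.05 once the first is significant. Power for each outcome under Holm is therefore at least 84.2% and at most 90.2% on these inputs.

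**The case against.** **The inflation is conditional.** No section says that one significant outcome is enough, and the aims join pain and function with the word *and*, which may suggest that both are needed. This stands. A reader might infer from the general threshold that the trial's error rate simply is nearly 10%, but the protocol does not support that. The figure needs an either-outcome rule, and 9.75% also needs independent tests. Both outcomes are reported by the same patients, so some positive correlation is likely and 9.75% is a ceiling. The wording of the aims does not settle the rule either, and if both outcomes must be significant, the stated 90% no longer describes success.

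**The time-points add nothing to the primary claim.** A reader might count six primary tests, two outcomes at three visits, and arrive at a much larger error rate. The protocol rules this out by naming 10 weeks as the single primary time-point, so weeks 5 and 26 are already outside the primary claim.

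**Multiplicity is often left to the analysis plan.** This would answer a complaint that the article is merely silent, but the article is not silent. It fixes an unadjusted 0.05 for all analyses, and a later adjusted procedure would contradict that sentence.

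**The 5% can be read as an alpha per outcome.** It can, and on that reading the sample size section contradicts nothing. It still leaves the error rate or the power of the overall conclusion unstated.

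**Conclusion.** The point holds in conditional form. The protocol fixes two unranked primary tests at 0.05 each and sizes the trial with one undivided 5% alpha and 90% power, without saying how the two results combine. The consequence is one of two things:

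- a family-wise false positive rate of up to 9.75% if either outcome can carry the claim (about 8.3% to 9.5% for correlations of 0.7 down to 0.3); or
- joint power of about 81% to 86% if both must be significant (correlations of 0 to 0.8), with the error at or below 5%.

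The ranges rest on assumed correlations, and the joint power also rests on 90% for each outcome. This is a moderate defect in the confirmatory claim. It can be corrected in the text and should be corrected before allocation is unblinded.

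**What to change.** In the Data analysis section, replace the general threshold, for the two primary outcomes only, with one of these rules:

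1. **Either outcome can support superiority.** Apply Holm's procedure to the two week-10 group contrasts: compare the smaller p-value with 0.025 and, if it is significant, the larger with 0.05. This holds the family-wise error at 5%.
2. **Both outcomes are required.** State that the trial is positive only if both week-10 contrasts are significant, keep 0.05 for each, and restate the planned power as joint power with the correlation assumed.

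Either rule takes one sentence; the second also needs a revised power statement.

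The cost of the first rule is the drop from 90.2% to 84.2% at the 0.025 step. That figure applies to the ANOVA test used for the sample size (f = 0.2, three measurements, assumed correlation 0.5, 178 evaluable); the protocol gives no power for the week-10 mixed-model contrast itself. The cost of the second rule is the lower joint power. Neither rule requires a change to the 210 participants.

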#### Primary analysis

The between-group differences for the primary outcomes considering the change in pain intensity and functionality from baseline to each 5, 10- and 26-weeks after randomisation will be calculated using mixed linear models using the interaction terms of treatment group versus time. The pain intensity and functionality will be investigated in separate models.

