#### Secondary analysis

The between-group differences for the secondary outcome considering the change in neuropathic symptoms, sciatic neurodynamic, conditioned pain modulation, and psychosocial factors from baseline to each 5, 10- and 26-weeks after randomisation will be calculated using mixed linear models using the interaction terms of treatment group versus time.

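### The primary and secondary models take the effect as change from baseline with no stated baseline adjustment, which gives up precision that the baseline score already collected could recover at no cost

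*Protocol article*

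**What the plan says.** The Primary analysis section sets the scale of the effect, "considering the change in pain intensity and functionality from baseline to each 5, 10- and 26-weeks after randomisation", and fits pain and function in separate models. The Secondary analysis section uses the same construction for its outcomes: the differences "will be calculated using mixed linear models using the interaction terms of treatment group versus time". The section on outcome measures fixes the main visit: "The follow-up assessment at 10 weeks after randomisation will be considered the primary time-point".

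No baseline covariate and no constraint of equal baseline means appears in the Primary analysis, Secondary analysis, Data analysis or Sensitivity analysis sections. The sample size section counts the initial visit as one of three repeated evaluations. This fits a model in which baseline is a level of time.

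**The concern.** If baseline is one of the time levels and each arm has its own free baseline mean, the week-10 interaction with complete data is the difference between arms in mean change. That contrast carries the full noise of the baseline measurement whatever the strength of its relation to follow-up. Adjusting for baseline uses only as much of it as the data support.

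At stake are the width of the confidence intervals and the power for both primary outcomes and for the continuous secondary outcomes. There is also a conditional effect. When the slope of follow-up on baseline is below 1, a change score over-corrects a chance baseline imbalance, so the arm that starts worse by chance tends to look better.

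**Working it through.** **Inputs.** From the sample size section: effect size 0.2, power 90%, alpha 0.05, 2 groups, 3 evaluations, 15% loss, 105 per group (210 in total). The correlation rho and the SDs are not given, so they are assumed below.

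**The plan's own figure.** The section says "An estimated small effect size of 0.2 [73] in a repeated-measures analysis of variance (ANOVA) was considered". Take 0.2 as Cohen's f and rho = 0.5 (assumed) in the between-groups test of a repeated-measures ANOVA:

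- Noncentrality = f² × N × m / (1 + (m − 1) × rho) = 0.04 × 178 × 3 / 2 = 10.68, with 1 and 176 degrees of freedom. Power is 0.9015, so N = 178.
- Allowing for loss: 178 / 0.85 = 209.4, rounded up to 210. This matches.

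With two equal groups f = 0.2 is d = 0.4, and 178 / 2 = 89 evaluable per arm. The within-between interaction test at f = 0.2 gives 56, or 66 after loss, which does not match. The stated 90% therefore belongs to a test averaged over three evaluations, not to the planned week-10 interaction.

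**Variance of the two contrasts.** Let s0 and s1 be the baseline and week-10 SDs. Per arm and per participant:

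- Change: s0² + s1² − 2 × rho × s0 × s1
- Baseline-adjusted: s1² × (1 − rho²)
- Change minus adjusted: (s0 − rho × s1)²

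The excess is never negative. It is zero only if s0 = rho × s1, that is, if the slope rho × s1 / s0 equals 1. With equal SDs the ratio adjusted/change is (1 + rho) / 2.

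**Numbers.** s1 = 1, n = 89 per arm, standard error = √(2 × variance / 89), power from the noncentral t with d = 0.4 in units of s1, two-sided 5%.

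| s0 | rho | Variance, change | Variance, adjusted | Ratio adjusted/change | Power, change | Power, adjusted |
|---|---|---|---|---|---|---|
| 1.0 | 0.3 | 1.40 | 0.91 | 0.65 | 61.1% | 79.4% |
| 1.0 | 0.5 | 1.00 | 0.75 | 0.75 | 75.6% | 86.5% |
| 1.0 | 0.7 | 0.60 | 0.51 | 0.85 | 92.9% | 96.0% |
| 0.8 | 0.3 | 1.16 | 0.91 | 0.78 | 69.3% | 79.4% |
| 0.8 | 0.5 | 0.84 | 0.75 | 0.89 | 82.5% | 86.5% |
| 0.8 | 0.7 | 0.52 | 0.51 | 0.98 | 95.7% | 96.0% |

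With equal SDs the change-score interval is 24.0%, 15.5% and 8.5% wider at rho 0.3, 0.5 and 0.7. At rho 0.5 adjustment is worth 89 / 0.75 = 119 evaluable per arm instead of 89.

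**Check on the model itself.** Generalised least squares on four visits (compound symmetry, equal SDs, 89 per arm) gives standard errors of 0.177 against 0.143 (rho 0.3), 0.150 against 0.130 (rho 0.5) and 0.116 against 0.107 (rho 0.7). The constrained-baseline and covariate models agree. In 100 simulated mixed-model fits at rho 0.5 the mean estimate was −0.385 under both, with mean standard errors of 0.149 and 0.129.

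**The case against.** **No adjustment is stated, but none is ruled out.** The article names a mixed model, interaction terms and separate models. It does not list the fixed effects. A constrained longitudinal model also reports group-by-time terms as change from baseline, so the wording is compatible with it, and an unseen analysis plan may already adjust. This stands as a limit on certainty. It does not remove the point: the article states an estimator, and its plain reading is the less precise one.

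**Nothing is invalid.** A reader might infer that the planned analysis is biased. The documents do not support that, because under randomisation both contrasts target the same difference. The over-correction concerns a given chance imbalance and needs a slope below 1.

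**The size rests on assumptions.** This stands. Equal SDs and rho are not in the article, and d = 0.4 depends on reading 0.2 as Cohen's f. At d = 0.2, with equal SDs and rho 0.5, power would go from 26.4% to 33.5%. The plan also imputes missing data under intention-to-treat, so 89 evaluable per arm is a simplification.

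**The entry limit on leg pain.** A reader might infer that enrolling only patients scoring above 3 lowers rho and so enlarges the loss. It works the other way. Under a linear relation, selection on baseline leaves the slope and residual variance unchanged and shrinks only s0. Suppose equal SDs of 1 and slope 0.5 before selection, and s0 cut to 0.7. Then s1² = 0.75 + 0.25 × 0.49 = 0.8725 and rho = 0.35 / 0.934 = 0.375. The change variance is 0.75 + 0.25 × 0.49 = 0.8725, so the true ratio is 0.75 / 0.8725 = 0.86. The equal-SD formula would give (1 + 0.375) / 2 = 0.69. The limit therefore tends to reduce the loss for leg pain, and it sets no bound on the functional scale.

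**Conclusion.** The point holds as a free improvement. As written, the plan's contrast is unbiased but never more precise, apart from one degree of freedom, than one adjusted for a baseline score the trial already collects. Under 89 evaluable per arm and d = 0.4, the power forgone at week 10 is about 18, 11 and 3 percentage points at rho 0.3, 0.5 and 0.7 with equal SDs. It is about 10, 4 and less than 1 points if the baseline SD is 0.8 of the follow-up SD. These are illustrations over assumed values, not properties of this trial. For leg pain the equal-SD figures are better read as the upper end. The point covers both primary outcomes and the continuous secondary outcomes only. It falls away if the full analysis plan already adjusts for baseline or constrains the baseline means.

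**What to change.** In the Primary analysis section, and in the Secondary analysis section for continuous outcomes, replace the model sentence with one of two equivalents:

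- a mixed model for the 5-, 10- and 26-week scores with baseline score (by time), time, group and group-by-time as fixed effects; or
- a constrained longitudinal model that includes baseline as a visit and gives both arms a common baseline mean.

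Report the adjusted between-group difference at each visit, with week 10 primary. If the full analysis plan already does this, say so in the article. Fix the choice before unblinding, so that it cannot be influenced by the results. The cost is one sentence in each section, with no new data and no additional participants.
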